#### Toxicity rates

The CTCAE v. 4.03, or the most recent update, will be used to assess all toxicity and adverse events observed during and after the completion of treatments [38]. Patients will be evaluated weekly by complete history taking, physical examination, and blood chemistry tests to determine the safety and toxicity of all treatments in this clinical trial. These evaluations will be conducted at each on-treatment appointment and at each clinical follow-up visit.

Efforts will be made to use bevacizumab as a first-line treatment for radiation-induced tumor/cerebral edema, based on its efficacy and minimal immunosuppressive effects [39–42]. For refractory cases or those in which bevacizumab is not available, dexamethasone will be used per routine protocols and noted in conjunction with serologic immune marker studies.

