### Treatment response assessments

#### Imaging

To assess the initial responses to the CIRT boost, MET/FET PET or MRS will be performed at 2 weeks after the initiation of CIRT in the experimental arm. To assess the overall treatment response, MET/FET PET or MRS will be performed at 4 weeks after the completion of PRT in both arms. The target lesion will be evaluated using the response assessment in neuro-oncology (RANO) criteria [43] with interpretation modifications [44, 45] and is summarized below:Complete response (CR): Complete disappearance of all tumors on consecutive computed tomography (CT) or MRI scans sustained for at least 1 month, without the use of steroids.Partial response (PR): An observed ≥ 50% decrease in the area of contrast enhancement on consecutive CT or MRI sustained for at least 1 month. Doses of steroids must be stable or decreased, and the patient must be neurologically stable.Progressive disease (PD): An observed ≥ 25% increase in the area of contrast enhancement or any new tumor on CT or MRI.Stable disease (SD): All other situations.

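### The response criteria condition on steroids only, while the protocol's first-choice oedema drug is bevacizumab, so a drug effect on enhancement can be scored as tumour response

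*Protocol article*

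**What the plan says.** Two neighbouring sections of the protocol article bear on this.

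- **Oedema treatment (Toxicity rates).** "Efforts will be made to use bevacizumab as a first-line treatment for radiation-induced tumor/cerebral edema". Dexamethasone comes second, for oedema that does not respond or when bevacizumab cannot be had. In those cases "dexamethasone will be used per routine protocols and noted in conjunction with serologic immune marker studies". No arm is exempted.
- **Response categories (Treatment response assessments, Imaging).** Complete response is disappearance of all tumour, "sustained for at least 1 month, without the use of steroids". Partial response is a 50% or greater "decrease in the area of contrast enhancement on consecutive CT or MRI sustained for at least 1 month", with the rider "Doses of steroids must be stable or decreased, and the patient must be neurologically stable". Progressive disease is a 25% or greater "increase in the area of contrast enhancement or any new tumor on CT or MRI". Everything else is stable disease. The section applies the RANO "criteria [43] with interpretation modifications [44, 45] and is summarized below".

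Bevacizumab appears in none of the four categories. Study objectives lists response rates, PFS and tumour response as secondary for Phase III. Outcome analyses describes the PFS analysis as exploratory.

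**The concern.** A steroid condition in a response rule exists because treating oedema can change the scan without changing the tumour. This protocol accepts that reasoning and builds it into complete and partial response. It then names a different drug as the preferred oedema treatment, so the condition covers the second choice and not the first. A patient given bevacizumab alone is off steroids and satisfies the condition automatically.

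At stake is the meaning of the response rate. Some of what is counted as tumour response could be a drug effect on enhancement. In the other direction, a rise in enhancement that would have been called progression could be masked for a time. If the two arms used the drug to different extents, the comparison of response between them would be biased.

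**Working it through.** **1. Which drug is covered by which rule**

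| Category | Imaging measure as printed | Steroid condition | Bevacizumab condition |
|---|---|---|---|
| CR | all tumour gone, held at least 1 month | none in use | none stated |
| PR | enhancing area down 50% or more, held at least 1 month | dose stable or lower | none stated |
| PD | enhancing area up 25% or more, or new tumour | none stated | none stated |
| SD | all other cases | none stated | none stated |

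A patient on bevacizumab and no dexamethasone passes the CR and PR drug conditions. A patient who needs both drugs is still caught by the steroid condition. The one-month confirmation does not remove the problem if the drug, or its effect, lasts beyond a month.

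**2. Is a difference between arms plausible?** The only stated figures are the cumulative brain doses in Table 1 (α/β = 3). With BED = n·d·(1 + d/3) and EQD2 = BED/(1 + 2/3):

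- Proton course alone: 60 × (1 + 2/3) = 100.0, and 100.0/(5/3) = 60.0 GyE.
- Plus 6 GyE in 2 fractions: 100 + 6 × 2 = 112.0, giving 67.2 GyE.
- Plus 9 GyE in 3 fractions: 100 + 9 × 2 = 118.0, giving 70.8 GyE.
- Plus 18 GyE in 3 fractions: 100 + 18 × 3 = 154.0, giving 92.4 GyE.

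These reproduce Table 1. For boosts of 9 to 18 GyE the nominal EQD2 is 18% to 54% above control (70.8/60.0 and 92.4/60.0). More oedema treatment in the boost arm is therefore plausible, but no oedema or bevacizumab rate is given for either arm.

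**3. Illustration of size.** All inputs here are assumptions, because the document gives none:

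- true response r = 20% in both arms;
- bevacizumab use b of 10% in control and 10%, 20% or 30% in the boost arm;
- a share q of 30% or 50% of treated non-responders scored as responders.

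Scored rate = r + (1 − r)·b·q. False difference = (1 − r)·(b_boost − b_control)·q.

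| Use, control vs boost | q | Control scored | Boost scored | False difference |
|---|---|---|---|---|
| 10% vs 10% | 30% | 22.4% | 22.4% | 0 |
| 10% vs 10% | 50% | 24.0% | 24.0% | 0 |
| 10% vs 20% | 30% | 22.4% | 24.8% | 2.4 points |
| 10% vs 20% | 50% | 24.0% | 28.0% | 4.0 points |
| 10% vs 30% | 30% | 22.4% | 27.2% | 4.8 points |
| 10% vs 30% | 50% | 24.0% | 32.0% | 8.0 points |

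With 122 patients in the boost arm, 2.4 to 8.0 points is about 3 to 10 patients (0.024 × 122 = 2.9; 0.080 × 122 = 9.8). At 30% true response the same unequal-use inputs give 2.1 points (0.7 × 0.10 × 0.3) to 7.0 points (0.7 × 0.20 × 0.5). With equal use both arms are inflated by the same 2.4 to 4.0 points at 20% true response, and the difference is zero.

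**The case against.** The strongest reply is that the printed categories are a short summary in a journal article. The governing criteria are RANO with two cited modifications, which are not shown and may already deal with bevacizumab. That stands as a limit: the document cannot settle it. It does not remove the point. The summary sets out drug conditions explicitly and includes only steroids, and a reader cannot assume that the missing condition sits in a reference.

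Several stronger readings are tempting and are not supported:

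- **That the boost arm will receive more bevacizumab.** This is inference from dose. Table 3 confines the boost to the gross tumour volume, so the Table 1 figures do not describe brain outside that volume. The Phase I dose rule also screens out doses with repeated severe acute toxicity. If the boost itself increased enhancement, that could be read as progression and count against it.
- **That most patients with oedema will receive bevacizumab.** The text promises efforts only and allows for the drug not being available.
- **That bevacizumab use goes unrecorded.** The sentence on noting dexamethasone concerns immune markers. Recording of other drugs is commonly left to the full protocol.
- **That PFS rests on contrast enhancement.** Its definition asks for recurrence confirmed by imaging and names neither enhancement nor RANO.
- **That a particular false-positive rate follows.** Outcome analyses assigns Fisher's exact test to adverse events, and no test is named there for response.

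It is also fair to say that PR requires neurological stability as well as shrinkage, that PD includes new tumour, and that response is assessed by PET or spectroscopy too. These narrow the gap but do not close it.

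**Conclusion.** The mismatch is real on the printed text: the drug condition in CR and PR covers the fallback oedema drug and not the preferred one. It affects the secondary response endpoint and may affect the exploratory PFS analysis through delayed progression calls. Measurement of overall survival is untouched.

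The size is not known. Under the assumptions shown, the false difference is about 2 to 8 percentage points in favour of the boost if that arm uses more bevacizumab, and about zero if use is equal. In the latter case both response rates are still too high. The conclusion assumes that bevacizumab can reduce enhancement without a matching tumour effect. The protocol does not say this; it cites only the drug's efficacy for oedema and its small immunosuppressive effect. It also assumes that the unseen modifications do not already cover the case. A reader might infer that the plan is biased towards the boost; the documents support only that it could be.

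**What to change.** 1. In the Imaging section, extend the drug conditions to bevacizumab. For CR: no steroids and no bevacizumab. For PR: neither drug started nor increased since the reference scan. If the cited modifications already contain such a rule, say so in one sentence instead.
2. Make bevacizumab start and stop dates available to those who score response.
3. Report bevacizumab use by arm next to the response and PFS results, so that a reader can judge whether unequal use could explain a difference.
4. Do not rely on censoring PFS at the start of bevacizumab. Patients who start it are likely to have symptomatic oedema that may accompany progression, so that censoring is probably informative. If it is run, label it a sensitivity analysis and state that limit.

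The cost is one sentence in the response definition, access to two dates per course of drug, and one descriptive table. Some patients will become non-responders or not evaluable, so response rates may be slightly lower. The change concerns how scans are classified and leaves patient care as it is.

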### Treatment response assessments

#### Imaging

To assess the initial responses to the CIRT boost, MET/FET PET or MRS will be performed at 2 weeks after the initiation of CIRT in the experimental arm. To assess the overall treatment response, MET/FET PET or MRS will be performed at 4 weeks after the completion of PRT in both arms. The target lesion will be evaluated using the response assessment in neuro-oncology (RANO) criteria [43] with interpretation modifications [44, 45] and is summarized below:Complete response (CR): Complete disappearance of all tumors on consecutive computed tomography (CT) or MRI scans sustained for at least 1 month, without the use of steroids.Partial response (PR): An observed ≥ 50% decrease in the area of contrast enhancement on consecutive CT or MRI sustained for at least 1 month. Doses of steroids must be stable or decreased, and the patient must be neurologically stable.Progressive disease (PD): An observed ≥ 25% increase in the area of contrast enhancement or any new tumor on CT or MRI.Stable disease (SD): All other situations.

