### Induction CIRT boost rationale

The novel approach of administering the CIRT boost prior to the initiation of standard, low-LET-based chemoradiotherapy has the following multiple theoretical advantages:Overcoming hypoxia. In the postoperative setting, the number of residual tumor cells and level of hypoxia are at their greatest extent, whereas CIRT can overcome such hypoxic conditions [29];Targeting glioma stem cells earlier in the treatment course. This enables the radiation-naïve stem cells to receive large-fraction doses of the more-effective high-LET irradiation before they can develop radio-resistance to smaller factions of low-LET radiotherapy;Altering the cell death mechanisms/immunogenicity. CIRT can shift the pro-/anti-tumor immunologic balance towards anti-tumor immunity at the beginning of radiotherapy, as opposed to being given after the immunosuppressive TMZ and conventional fractions of low-LET radiotherapy have been delivered;Treatment compliance. Patients are more likely to receive the entire prescribed CIRT dose if it is given first. Fatigue and toxicity of the 30-fraction PRT course could potentially dissuade continued treatment;CIRT responses. Assessing the CIRT-specific responses (imaging and immunologic assays) is less confounded by standard PRT. The biological effect of CIRT differs from that of low-LET PRT and the administration of CIRT boost prior to standard chemoradiotherapy would reduce the interference of other factors to detecting CIRT-specific responses.

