#### Phase III

##### Experimental arm

A total of 122 patients will be enrolled into this arm and undergo an induction CIRT boost to the residual gross tumor volume. The dose of the induction boost will be determined in Phase I of the trial. One week after the first fraction of the induction boost, a standard PRT (60 GyE in 30 fractions) with concurrent daily oral administration of TMZ at 75 mg/m^2^ will commence.

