##### Serologic immune markers

To ascertain the specific immune response profile to the induction CIRT boost, all patients enrolled into the Phase III study will have their blood samples investigated before irradiation to establish the baseline profile of serologic immune markers (detailed in Table 2 and between the fifth and sixth fractions of PRT to determine the changing profile. Those who receive the induction CIRT boost will have an additional serologic marker detection between the last fraction of the boost and the first proton fraction. The overall Phase III schema is illustrated in Fig. 1.

**Table 2 Tab2:** Serologic immune markers of GBM

Marker	Function/correlative findings	Assay
Pro-inflammatory/anti-tumor		
IL-1β	Stimulates cytotoxicity; serum levels decrease during low-LET radiotherapy [55]	Serum ELISA
IL-6	Pro-inflammatory cytokine, defective expression from lymphocytes in patients with glioma [56]	Serum ELISA
TNF-α	Promotes cell-directed cytotoxicity; reduced levels are associated with GBM [57]	Serum ELISA
CD3+ lymphocytes	Direct immune-mediated cytotoxicity; increased levels are associated with prolonged survival [58]	Flow cytometry
CD8+ lymphocytes	Direct immune-mediated cytotoxicity, increased levels are associated with prolonged survival [58]	Flow cytometry
Anti-inflammatory/pro-tumor		
IL-4	Induces immunosuppression and tumor tolerance; high levels are associated with GBM [57]	Serum ELISA
IL-10	Induces immunosuppression and tumor tolerance; high levels are associated with GBM [57]	Serum ELISA
TGF-β	Promotes proliferation and immune escape of GBM [59]	Serum ELISA
Regulatory T cells	Secrete IL-10 and TGF-β, suppress CD8-dependent tumor-specific cytotoxicity, and elevated in peripheral blood of GBM patients [60]	Flow cytometry

*GBM* glioblastoma, *IL* interleukin, *TNF*-*α* tumor necrosis factor-α, *TGF*-*β* transforming growth factor-β, *LET* linear energy transfer, *ELISA* enzyme-linked immunosorbent assay

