### TMZ dosing and schedule

Conventional oral chemotherapy with TMZ (75 mg/m^2^) will commence on the first day of PRT in both arms. TMZ will not be administered during the CIRT boost in the experimental arm so as not to suppress the desired shift towards an anti-tumor immune response and the effect against glioma cells that have infiltrated the brain parenchyma at a distance from the primary tumor site.

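### The two-week scan described as showing the initial response to the carbon ion boost also captures about five proton fractions and a week of temozolomide, so it cannot show the response to the boost alone

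*Protocol article*

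**What the plan says.** Under Treatment response assessments, Imaging, the protocol article sets two scans by MET/FET PET or MRS. The early one has a stated purpose and date: "To assess the initial responses to the CIRT boost, MET/FET PET or MRS will be performed at 2 weeks after the initiation of CIRT". Only the experimental arm is named for it. The later one, four weeks after proton therapy ends, is for overall response and covers both arms.

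The treatment dates are elsewhere:

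- Phase III, Experimental arm: "One week after the first fraction of the induction boost, a standard PRT" course of 30 fractions begins, with daily TMZ.
- TMZ dosing and schedule: TMZ "will commence on the first day of PRT in both arms".
- Radiotherapy planning: carbon ion and proton sessions are given once daily, five days a week.

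The section on the rationale for the induction boost lists the assessment of carbon-ion-specific responses, by imaging and by immune assays, among the advantages of giving the boost first. It says that "the administration of CIRT boost prior to standard chemoradiotherapy would reduce the interference of other factors to detecting CIRT-specific responses".

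For the blood markers (Serologic immune markers, Phase III), the experimental arm has an "additional serologic marker detection between the last fraction of the boost and the first proton fraction". Both arms are also sampled after the fifth and before the sixth proton fraction.

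**The concern.** The Imaging section assigns the two-week scan to the boost without qualification, yet the protocol's own dates put it a week into chemoradiotherapy. Any change from baseline then combines three exposures: boost, early proton therapy and TMZ.

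Two designs could separate them: a reading before the first proton fraction, or a control-arm reading at the same proton exposure. The blood schedule has both. The imaging schedule, as written, has neither.

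What is at stake is a conclusion about mechanism. If the two-week result were reported as the response to carbon ions, some of the effect of standard treatment could be credited to the boost. Tumour response by imaging is a secondary objective, so the point bears on what the trial may conclude there and not on the primary comparison of overall survival.

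**Working it through.** **Reproducing Table 1.** The formula is BED = n·d·(1 + d/(α/β)), with α/β = 10 for tumour. Proton therapy alone gives 60 × 1.2 = 72.0 GyE. Adding the boost:

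- 3 × 2: 72.0 + 6 × 1.3 = 79.8
- 3 × 3: 72.0 + 9 × 1.3 = 83.7
- 4 × 3: 72.0 + 12 × 1.4 = 88.8
- 5 × 3: 72.0 + 15 × 1.5 = 94.5
- 6 × 3: 72.0 + 18 × 1.6 = 100.8

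All six tumour values agree with the table, so the same formula can be used for the dose delivered by the scan date.

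**Calendar.** Let the first boost fraction be day 0. Proton therapy and TMZ start on day 7 and the scan is on day 14. Days 7 to 13 are seven consecutive days and contain five weekdays whatever the starting weekday. Without holidays or interruptions, that gives:

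- 5 proton fractions, 5 × 2 = 10 GyE (6 fractions, 12 GyE, if the scan follows that day's session)
- 7 daily TMZ doses

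**Dose delivered by the scan.** Five proton fractions give a tumour BED of 10 × 1.2 = 12.0 GyE. The proton share is 12.0/(12.0 + boost BED). For six fractions, 12 × 1.2 = 14.4 replaces 12.0.

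| Boost (GyE) | Boost BED (GyE) | Proton share, 5 fractions | Proton share, 6 fractions |
|---|---|---|---|
| 9 | 11.7 | 12.0/23.7 = 51% | 55% |
| 12 | 16.8 | 12.0/28.8 = 42% | 46% |
| 15 | 22.5 | 12.0/34.5 = 35% | 39% |
| 18 | 28.8 | 12.0/40.8 = 29% | 33% |

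For the 6 GyE fallback the boost BED is 7.8 GyE and the five-fraction share is 12.0/19.8 = 61%. TMZ is not counted in any of these.

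**Comparison with a boost given last.** If the boost followed the full proton course, 72.0 GyE of proton BED would already be in place. The proton share would be 72.0/83.7 = 86% at 9 GyE and 72.0/100.8 = 71% at 18 GyE. Giving the boost first lowers this to 51% and 29% at the two-week scan.

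**Window before proton therapy.** A course starting Monday to Wednesday has boost fractions on days 0, 1 and 2, which leaves 5 days to day 7. A Thursday start (days 0, 1, 4) or a Friday start (days 0, 3, 4) leaves 3 days. A scan in this window would follow no proton fraction and no TMZ dose.

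**The case against.** The best defence is that the rationale section promises less than a pure carbon ion reading. It speaks of reduced interference, and that is true of this schedule: 12.0 GyE of proton BED precedes the scan, against 72.0 GyE had the boost come last. A reader might infer that the scan date cancels the advantage of giving the boost first. The protocol's figures do not support that, since the advantage is reduced and not lost.

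Second, a share of BED is not a share of imaging change. The boost is finished before day 7, while the proton fractions fall in the week just before the scan, and the protocol says nothing about the lag between dose and visible change. A reader might take 29% to 51% as the part of the signal due to protons, but the documents give no basis for that.

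Third, the missing control-arm scan is an absence from the text of a condensed article. Fig. 1 is not shown, and its caption mentions imaging assessment of every patient and MRI techniques that the text does not describe. The statement must therefore be limited to the text.

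Fourth, a reader might infer that this scan enters the between-arm response or PFS comparison. The plan does not put it there. Overall response is assigned to the scan after proton therapy in both arms, and PFS rests on routine follow-up or symptom-directed imaging.

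Last, two weeks may have been chosen so that a change has time to appear. That could justify the date, but the article does not say so, and it would not justify attributing the result to the boost alone. All of this narrows the point. None of it changes the fact that the stated purpose and the stated dates do not match.

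**Conclusion.** The point holds in a limited form. As written, the two-week scan measures early response to the boost plus about five proton fractions and a week of TMZ, and the text provides nothing that would separate the parts. At every boost level the added exposure is substantial: 12.0 GyE of proton BED against 11.7 to 28.8 GyE from the 9 to 18 GyE boosts, before TMZ.

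This assumes uninterrupted treatment on the stated dates, daily TMZ from the first proton day, and Table 1's α/β of 10. It also assumes that the full schedule contains no early control-arm scan. The size and direction of any bias in the imaging result cannot be derived from the documents.

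Overall survival, its sample size, the interim analysis and the two-arm response assessment after proton therapy are unaffected.

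**What to change.** Reconcile the sections on Induction CIRT boost rationale, Phase III Experimental arm, TMZ dosing and schedule, and Imaging. In Imaging, redefine the two-week scan as early response to the boost plus the first week of proton therapy and TMZ. State that it is described in the experimental arm only and that no response will be attributed to carbon ions alone. This is a change of wording and costs nothing.

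As an option for the sponsor to weigh, the scan could move to the window between the last boost fraction and the first proton fraction, where the blood sample is already taken. The number of scans stays the same. The drawback is that only about 3 to 5 days would have passed since the boost, so the visible change may be smaller.

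If Fig. 1 or the full protocol does contain a control-arm scan at the same proton exposure, the Imaging section should say so. No change of treatment timing is implied by either route.

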### Patient selection

#### Inclusion criteria

Patients who meet all of the following criteria will be considered for recruitment into this trial:Histologically confirmed, unifocal, supra-tentorial primary AA or GBM;Residual, clinically measurable tumor up to 5 cm in the largest dimension assessed by postoperative MET/FET PET, MR spectroscopy (MRS), or MRI;Able to determine the *MGMT* promoter methylation status;Indication for adjuvant radiotherapy with concurrent TMZ administration;Age ≥ 18 years;Karnofsky performance score ≥ 60;Ability to understand the purpose and content of the clinical trial;Written informed consent with required signature prior to enrollment and initiation of the treatment.

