#### Exclusion criteria

Patients who present with any of the following criteria will not be included in this trial:Patient’s refusal to follow the trial protocols;Severe pulmonary hypertension, cardiovascular disease, peripheral vascular disease, severe chronic heart disease, and other complications that may interfere with radiotherapy;Previous radiotherapy to the brain;Previous malignancy requiring cytotoxic therapy within 5 years prior to enrollment;No residual, clinically measurable disease observed on postoperative MET/FET PET, MRS or MRI;A time interval > 8 weeks between surgery and the initiation of radiotherapy;Not yet recovered from toxicities of prior treatments;Pregnant or lactating women;Participation in another clinical study or in an observation phase of a competing trial.

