### Radiotherapy planning

Target volume delineation: Numerous studies have indicated that the use of MET/FET PET, MRS in conjunction with MRI was superior to MRI alone in determining the extent of malignant involvement [33–36]. Therefore, tumor areas presented on the MET/FET PET, MRS as well as the traditional contrast enhancement and fluid-attenuated inversion recovery (FLAIR) abnormality indicative of residual non-enhancing tumor (edematous FLAIR signal that does not resolve after surgical decompression) will be used to determine the gross tumor volume (GTV).

The clinical target volume (CTV) receiving 60 GyE irradiation (CTV60) will be delineated with a 0.5-cm margin expansion from the GTV and will be the principle planning target volume of PRT. During PRT, a secondary CTV of 50 GyE in total will be given. The CTV50 will be delineated with a 1.5-cm expansion from the GTV. The volumes, doses, and delineations are summarized in Table 3.

**Table 3 Tab3:** Target Volume delineations and radiotherapy planning of GBM and AA

Radiotherapy	Target volume	Delineation	Dose/fractionation	Minimal dose coverage
CIRT boost	GTV	MET/FET PET or MRS abnormality, contrast enhancement, FLAIR abnormality representing residual tumor	3.00-6.00 GyE × 3 Fx	95%
PRT	GTV	MET/FET PET or MRS abnormality, contrast enhancement, FLAIR abnormality representing residual tumor	N/A*	N/A*
	CTV60	GTV + 0.5 cm margin	2.00 GyE × 30 Fx	95%
	CTV50	GTV + 1.5 cm margin	1.67 GyE × 30 Fx	95%

*GBM*: glioblastoma, *AA* anaplastic astrocytoma, *CIRT* carbon ion radiotherapy, *GTV* gross tumor volume, *MET/FET PET* C-methionine/18F-fluoro-ethyl-tyrosine positron emission tomography, *MRS* magnetic resonance spectroscopy, *FLAIR* fluid-attenuated inversion recovery, *N/A* not applied, *GyE* gray-equivalents, *Fx* fraction, *PRT* proton radiotherapy, *CTV60/50* clinical target volume receiving 60/50 GyE irradiation

* N/A: Since the GTV of PRT is not a target volume to give prescription dose, so “N/A” is marked in these cells

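### Partial response and progression by growth are defined by contrast-enhancing area on CT/MRI, but entry and target rules accept non-enhancing tumour and the scheduled PET/MRS response scans have no printed scoring rule

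*Protocol article*

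**What the plan says.** **Entry.** The inclusion criteria ask for "Residual, clinically measurable tumor up to 5 cm in the largest dimension assessed by postoperative MET/FET PET, MR spectroscopy (MRS), or MRI". The exclusion criterion uses the same three modalities: "No residual, clinically measurable disease observed on postoperative MET/FET PET, MRS or MRI". Neither mentions contrast enhancement.

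**Target.** Under Radiotherapy planning, the gross tumour volume includes PET and MRS abnormality, contrast enhancement, and "fluid-attenuated inversion recovery (FLAIR) abnormality indicative of residual non-enhancing tumor"; Table 3 repeats this. The same section says that PET and MRS used together with MRI "was superior to MRI alone in determining the extent of malignant involvement".

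**Response scans.** Under Treatment response assessments, Imaging, the early scan is "MET/FET PET or MRS will be performed at 2 weeks after the initiation of CIRT in the experimental arm" and the overall scan is "MET/FET PET or MRS will be performed at 4 weeks after the completion of PRT in both arms".

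**Response categories.** The same section names the RANO criteria with modifications from cited sources and summarises them in four categories, all read on CT or MRI:
- Complete response (CR): every tumour gone, sustained for at least a month.
- PR: "An observed ≥ 50% decrease in the area of contrast enhancement on consecutive CT or MRI", also sustained for at least a month.
- PD: enhancing area up by 25% or more, or any new tumour.
- SD: everything else.

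**Endpoint and other imaging.** The Phase III objectives list response rates and tumour response as secondary, with tumour response based on PET or MRI. The Follow-up section schedules brain MRI at every visit, the first two at 1 and 3 months after radiotherapy.

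**The concern.** The protocol expects tumour that enhancement does not show: it admits patients on that basis and irradiates that tissue. It then measures shrinkage and growth by enhancing area alone. A rule that returns SD for a lesion that has clearly shrunk or grown gives a wrong result when it is followed as printed, so this is more than missing detail.

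The second problem is that the scan assigned to response and the rule for scoring it belong to different modalities. Response to the carbon ion boost on its own is one of the stated reasons for giving the boost first (Induction CIRT boost rationale), and the 2-week scan is the one meant to show it.

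What is at stake is the meaning of the secondary response endpoint, and whether the PET and MRS data can be summarised by any rule fixed in advance.

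**Working it through.** The plan gives no design figure for response. Its only design figure is 192 deaths for overall survival. With medians of 16 and 24 months, two-sided 5% and 80% power, Schoenfeld's formula gives 4 × (1.960 + 0.842)² / (ln 1.5)² ≈ 191. The figure reproduces, and nothing in this point touches it.

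**Step 1: can a patient enter without enhancing tumour?** Yes. Under the inclusion criterion any one of PET, MRS or MRI is enough. Even if the exclusion criterion were read to demand visibility on MRI, FLAIR is an MRI sequence, so a non-enhancing lesion would still qualify.

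**Step 2: apply the printed categories to a patient with no enhancing area at baseline.**

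| What happens to the lesion | Printed category | Reason |
|---|---|---|
| Non-enhancing lesion disappears | CR possible | CR refers to all tumours, not to enhancement |
| Non-enhancing lesion shrinks by half or more but remains | SD | PR needs a fall in enhancing area, and the baseline is zero |
| Non-enhancing lesion grows, nothing new | SD | a 25% rise from zero is undefined, and there is no new tumour |
| New tumour appears | PD | the new-tumour clause applies |

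The middle two rows are the fault: partial shrinkage and growth of the existing lesion both fall to SD.

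**Step 3: how many patients?** The share f with no enhancing residual tumour is not in the document. Assume 5–20%:
- 0.05 × 243 = 12.15, about 12 patients
- 0.20 × 243 = 48.6, about 49 patients

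**Step 4: effect on a response rate (illustration).** Assume a true response rate of 30% and, as the extreme case, that no non-enhancing patient reaches CR. The observed rate is then 0.30 × (1 − f):
- f = 5%: 0.30 × 0.95 = 28.5%
- f = 20%: 0.30 × 0.80 = 24%

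Any CR among these patients makes the shortfall smaller. Both the 30% and the range of f are assumptions.

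**Step 5: match scan to rule.**

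| Time point | Scan named for response | Printed rule for that scan | MRI scheduled in the text |
|---|---|---|---|
| 2 weeks after start of boost (experimental arm) | PET or MRS | none | none |
| 4 weeks after proton therapy (both arms) | PET or MRS | none | yes, at the 1-month visit |
| 3 months after radiotherapy | none named | CT/MRI categories could be applied | yes |

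The overall response can thus be scored from MRI that is already planned, but the Imaging section does not assign it to that MRI. At 2 weeks there is neither a PET/MRS rule nor an MRI in the text.

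**The case against.** The best defence is that the article only summarises RANO with cited modifications, and that the full protocol or those sources may deal with non-enhancing disease and with PET and MRS. They are not shown, so this may be so. But the printed catch-all sends such cases to SD, so even then the two must be reconciled. The defence also points out that MRI at 1 and 3 months suits the requirement for consecutive scans at least a month apart, that the objectives name MRI as a basis for tumour response, and that the schema's multi-modal MRI includes both MRS and conventional MRI. This stands, and it confines the modality gap to the PET/MRS scans.

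A reader might infer more than the text supports:
- *Response and progression rest on enhancement alone.* They do not. CR covers all tumours, and PD includes any new tumour.
- *Some patients cannot be classified.* Every patient receives a category, because SD takes the remainder. The fault is misclassification.
- *No response can be scored at all.* The follow-up MRI can be scored.
- *Patients without enhancement are in CR before treatment, which inflates the response rate.* FLAIR-visible tumour is present on the baseline MRI and so is not CR. For tumour seen only on PET or MRS, disappearance still implies that something was there to disappear. An upward bias does not follow.
- *Baseline and follow-up will use different modalities.* That is only an inference from the word or; no passage says it.
- *Progression-free survival is biased.* Its definition uses recurrence confirmed by imaging and does not refer to the PD rule. The analysis is also exploratory.

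**Conclusion.** The point holds in a limited form. The printed rules misclassify partial shrinkage and growth of non-enhancing tumour as SD in patients whom the protocol deliberately admits, and the scheduled PET/MRS response scans have no printed scoring rule, most clearly at 2 weeks.

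The size is uncertain because it depends on a share that the document does not give: about 12–49 of 243 patients at the assumed 5–20%. The same category rules apply in both arms, and no bias between arms is shown. The consequence is confined to the secondary response endpoint; the survival comparison and its 192 events stand. It should be corrected, but it does not threaten the trial's main conclusion.

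**What to change.** 1. State that the response categories are read on the brain MRI already scheduled at 1 and 3 months after radiotherapy, against a pre-radiotherapy MRI. Target delineation already relies on contrast enhancement and FLAIR, so such imaging is part of planning.
2. Apply the enhancement-based PR and PD thresholds only to patients with measurable enhancing tumour on that baseline MRI, and report the response rate in that group. Replace the SD default for non-enhancing tumour with an explicit rule under which its clear growth counts as PD. If the cited modifications already contain such a rule, print it and align the SD category with it.
3. Report PET and MRS separately, as change from baseline within each patient on the same modality, or label them descriptive. This also settles the status of the 2-week scan.

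The cost is wording and case-report-form fields; no new post-treatment scans are needed. The response denominator becomes smaller: at the assumed 5–20%, it falls from 243 to between 243 − 12 = 231 and 243 − 49 = 194.
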